### Sample size

Approximately 300 participants each from Melbourne and from Canberra, Australia will be enrolled in ENVIS-ion. The sample size calculations were based on a) a pilot study of 144 older adults, in which acceptance of MR imaging was 88%, and which produced MR imaging estimates of change in relevant structural brain parameters over a two-year period; b) rate of change of WMH over 3 years from the PROSPER trial of adults aged 70 years or over [42]; and c) cautious interpretation of the report by Sato et al., in which treatment with around 300 mg/day of aspirin over one year reduced incident SBIs on MRI from 20.6% to 9.6% in 150 participants with non-valvular atrial fibrillation (i.e. a relatively higher risk group than in ENVIS-ion) [13,43]. Based on power calculations related to the primary hypothesis, we conservatively estimate the need for at least 230 per treatment arm to achieve a statistical power of 0.9 to show a relative risk reduction of 15% with a 2-sided α of 0.05.

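### The claim of 90% power for a 15% relative risk reduction with 230 per arm names no endpoint: read as silent brain infarction it fails, and read as white matter lesion change it uses the wrong measure and cannot be checked

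*Protocol article*

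**What the plan says.** The Sample size section of the protocol article makes a complete power statement. The trial needs "at least 230 per treatment arm to achieve a statistical power of 0.9 to show a relative risk reduction of 15" per cent, "with a 2-sided α of 0.05". The statement is tied to the primary hypothesis, without naming an endpoint, and the estimate is described as conservative.

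Three inputs are listed before it:

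- a pilot study of 144 older adults, which supplied estimates of structural brain change over two years;
- a three-year rate of change of WMH from a cited trial in adults aged 70 or over;
- a cautious reading of a report in which aspirin "reduced incident SBIs on MRI from 20.6% to 9.6% in 150 participants with non-valvular atrial fibrillation". The regimen there was "treatment with around 300 mg/day of aspirin over one year", and the article describes that population as "a relatively higher risk group than in ENVIS-ion".

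Only the third input comes with event rates. No mean or SD is printed for the first two. The first aim of the trial covers both WMH and SBI. The Statistical analysis section assigns continuous MRI changes to ANCOVA with baseline adjustment, and categorical variables to chi-square tests and logistic regression. The Abstract gives three years of treatment, 1:1 allocation and 600 participants.

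**The concern.** A relative risk reduction belongs to a yes/no outcome. Of the two components of the first aim, only the occurrence of SBI is of that kind, and SBI is also the only outcome with printed event rates. A reader will therefore apply the 15% to SBI. Those printed rates (20.6% and 9.6%) differ by far more than 15% in relative terms, so it is natural to ask whether 230 per arm can detect 15% at all.

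At stake is how a neutral result is read. If the stated power is taken at face value, a non-significant SBI comparison looks like good evidence against a 15% benefit. If the real power is a small fraction of 0.9, it is no such evidence. Calling the estimate conservative adds to the false reassurance.

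**Working it through.** **Inputs from the article.** Two-sided alpha 0.05 (z = 1.960); power 0.9 (z = 1.282); 230 per arm; 1:1 allocation; relative reduction 15%; printed control risk 20.6% over one year; trial follow-up three years; 600 enrolled, so 300 per arm.

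**Reading 1: the 15% refers to SBI (binary).** The pooled two-proportion formula is

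n per arm = [1.960·√(2·p̄(1−p̄)) + 1.282·√(p1(1−p1) + p2(1−p2))]² / (p1 − p2)², where p̄ is the mean of p1 and p2.

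Attempt to reproduce the plan's figure at the printed control risk:

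- p1 = 0.206, p2 = 0.85 × 0.206 = 0.1751, difference 0.0309, p̄ = 0.19055.
- n = (1.960 × 0.5554 + 1.282 × 0.5550)² / 0.0309² = 3,393 per arm, against the stated 230.
- Power at 230 per arm = Φ[(0.0309·√230 − 1.960 × 0.5554)/0.5550] = Φ(−1.117) = 0.13. With all 300 per arm it is 0.16.

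Standard variants do not close the gap:

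| Variant | n per arm |
|---|---|
| Unpooled variance | 3,390 |
| Continuity correction | 3,458 |
| One-sided test | 2,765 |
| 80% power | 2,535 |

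*Allowing for three years.* The 20.6% is a one-year figure. Compounded at a constant rate (an assumption), it becomes 1 − (1 − 0.206)³ = 0.499. A 15% reduction from there needs 929 per arm, and 230 per arm give 36% power (300 give 45%).

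*Where the claim would be true.* Solving the formula for n = 230 with p2 = 0.85·p1 gives p1 = 0.84, that is, about 84% v 71%. With 300 per arm the control risk would have to be about 78%.

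*Across control risks.* All risks below other than 20.6% are assumptions.

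| Control risk | Power at 230 per arm for a 15% reduction | n per arm needed for a 15% reduction | Reduction detectable at 90% power with 230 per arm |
|---|---|---|---|
| 10% | 8% | 7,839 | 73% |
| 20.6% | 13% | 3,393 | 52% |
| 30% | 19% | 2,079 | 43% |
| 50% | 36% | 927 | 30% |

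**Reading 2: the 15% refers to mean WMH change (continuous).** The formula is n per arm = 2·(1.960 + 1.282)²·(SD/difference)².

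- With n = 230, the detectable standardised difference is 3.242 × √(2/230) = 0.302.
- If the difference is 15% of the mean control change, then 0.15/(SD/mean) must be at least 0.302, so SD/mean must be at most 0.15/0.302 = 0.50. Here SD is the residual SD of change after baseline adjustment.
- Equivalently, the detectable reduction in mean change is about 30% × SD/mean.
- Power at 230 per arm for a 15% reduction is about 0.90 if SD/mean is 0.50, 0.57 if 0.75, 0.36 if 1.0 and 0.19 if 1.5. These ratios are assumptions; the article prints none.

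**The case against.** The strongest defence is that the 15% was never about SBI. Two of the three listed inputs are continuous change measures, WMH comes first in the first aim, and continuous MRI changes are to be analysed by baseline-adjusted ANCOVA. On that view the sentence is loosely worded and 230 per arm may be correct. Much of this stands. The WMH reading can be neither confirmed nor excluded, and nothing in the article shows whether an SD/mean ratio of 0.50 is hard or easy to meet. The missing SD is not itself a fault, since a condensed article may leave it to the full protocol. But the defence concedes that a risk measure has been attached to a quantity that is not a risk, so the sentence still needs correcting.

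A second defence is that the printed rates cover one year in a different population, while this trial runs for three. Longer follow-up does raise the cumulative risk. The article's own remark that the source group was at higher risk pulls the other way. Even at about 50%, power is 36% and the detectable reduction about 30%, twice the stated effect.

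A reader might also infer that 230 was derived from 20.6% v 9.6%, a 53% reduction, because 230 per arm give 91% power for that contrast. The article does not say so. The formula gives 221 per arm, or 239 with continuity correction, and other contrasts come as close: 50% v 35% gives 227. The article also says it interpreted that report cautiously. The origin of 230 is unknown, and the point does not depend on it.

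Finally, a confidence interval would show a careful reader how little a neutral SBI result excludes. That limits the harm but does not make the stated power correct.

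**Conclusion.** The power sentence is wrong as written, under either reading.

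- **For SBI**, the stated power is not delivered. At the printed 20.6% the required sample is about 15 times the stated one (3,393/230 = 14.8), and power is about 13% rather than 90%. At an assumed three-year risk of about 50% the shortfall is about fourfold (929/230 = 4.0), with power of about 36%. Only a control risk of about 84% would make the claim true, and no such rate is printed.
- **For WMH change**, the effect measure is misnamed. Whether 230 per arm suffice depends on an unprinted ratio, which must be at most about 0.50. It would go too far to say that the trial is underpowered for WMH: the article does not allow that conclusion, or the opposite one.

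The SBI figures rest on the standard two-proportion formula. They also assume that 20.6%, or its compounded value, is a fair guide to the control risk. The conclusion holds at every control risk well below 84%. Enrolment and the planned analyses are not affected.

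**What to change.** Keep 600 enrolled and rewrite the paragraph.

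1. Name the endpoint to which the 15% refers.
2. For SBI, state the assumed three-year control risk and the reduction that 230 per arm detect at 90% power, taken from the table above: about 73% at 10% risk, 52% at 20.6%, 43% at 30% and 30% at 50%. The figure quoted must match the three-year risk assumed, not the one-year rate by default.
3. For WMH, state the assumed mean three-year change in controls and the residual SD, and call the effect a relative reduction in mean change. Give the detectable size as about 30% × SD/mean.
4. Remove the 15% relative risk reduction and the word *conservatively* for SBI. Keep 15% for WMH only if the SD/mean ratio supports it.
5. Do not state that 230 came from 20.6% v 9.6% unless the sponsor's records show it.

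The cost is one reworded paragraph and, for SBI, a less favourable detectable effect. No further participants are needed.

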### Statistical analysis

Group descriptive statistics will be used to define the baseline characteristics of subjects randomized to aspirin and placebo groups. Continuous variable changes will be normalized prior to analysis and non-parametric methods will be used where required. Changes in continuous variables for both MRI and RVI over three years will be analyzed using analysis of covariance (ANCOVA) adjusting for baseline values (Aims 1,2 & 5). Chi-square and logistic regression analysis will be used to assess changes in categorical variables. Correlation and regression analysis will be used to determine the association between changes in MRI and RVI measures and the association of baseline cognitive measures with MRI and RVI parameters (Aims 3 & 4). Generalized linear models will be developed to determine whether age, gender, education, previous aspirin use and hypertensive status modify the treatment effects on MRI and RVI outcome measures (Aim 6).

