### Magnetic Resonance Imaging (MRI)

Brain MRI changes correlate with white matter ischaemia/infarction and MRI is commonly used to investigate the underlying mechanisms and predictors of dementia and cognitive decline [7]. MRI can assess brain structure changes using volumetric tissue measurements, or intensity-based lesion identification to quantify structural changes such as hyper-intense white matter lesions (WMH) or infarcts. The association of greater WMH volume with poorer cognitive performance remains a focus of ongoing research. While some studies have found that WMH presence and volume rather than location determines the presence of executive dysfunction in those who are non-demented, others have specifically related periventricular WMH to such cognitive dysfunction [12]. Silent brain infarcts (SBI) are frequently seen on MRI in healthy older adults and are associated with dementia incidence and cognitive decline as well as subsequent clinical stroke [13,14]. The Rotterdam Stroke Study found that the presence of SBIs at baseline more than doubled the risk of dementia [14]. In addition, the presence of SBIs at baseline was associated with poorer initial cognitive performance and a steeper decline in global cognition. Also, the incidence of SBI increased markedly with age and a prevalent SBI at baseline strongly predicted a new silent infarct on the second MRI [15]. The authors concluded that the cardiovascular risk factors for SBI are similar to those for stroke.

The preventive effects of aspirin on MRI-detected SBI and WMH have previously been investigated. A study by Sato et al. found that in patients with non-valvular atrial fibrillation (NVAF), and perhaps also those in sinus rhythm, aspirin may reduce SBIs [13]. Fujita et al. also reported a significant reduction in progression of WMH over 4 years with aspirin treatment for those with corrected platelet hyper-aggregability in a study of older, treated patients compared with age- and WMH-matched controls [10]

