### The ENVIS-ion trial

The ENVIS-ion trial is designed to determine whether;

a) low-dose aspirin reduces the development of WMH and SBI as assessed by MRI,

b) a reduction in changes in RVI parameters is observed with low-dose aspirin therapy,

c) changes in RVI parameters parallel changes in brain MRI,

d) baseline cognitive function correlates with baseline MRI and RVI parameters,

e) changes in cognitive function correlate with changes in brain MRI and RVI, and

f) factors such as age, gender, education or blood pressure influence the above associations.

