### Cognitive testing

Cognitive testing for the parent ASPREE trial consists of i) the Modified Mini-mental State examination as a test of general intellectual function, on which participants must score > 77/100 at entry [29]; ii) a single-letter ("F") Controlled Oral Word Association test (COWAT), which gives equivalent information to the longer 3-letter tests, as a measure of fluency [30]; iii) the Hopkins Verbal Learning Test-Revised as a measure of verbal anterograde episodic memory [31]; and iv) an alternative version of the Digit-Symbol Modalities test as a measure of psychomotor speed [32]. The Center for Epidemiological Studies - Depression Scale (CES-D) is also included in the ASPREE battery for later analysis as a covariate [33]. In addition to the cognitive function testing in ASPREE, ENVIS-ion participants will complete the Stroop test (Victoria version) as a measure of cognitive inhibition, and the Color Trails test, which is a non-language based test of sequencing, alternation and processing speed [32,34-36].

The emphasis on aspects of executive functioning (COWAT, Stroop, Color Trails) and processing speed (SDMT, Color Trails) reflects the typical neuropsychological pattern seen with cognitive impairment due to subcortical ischaemic damage [37], the focus of this study. The choice of test battery is based on the neuropsychological batteries suggested for assessment of vascular cognitive impairment [38]. Assessors will undergo standard training and assessment of the administration of tasks and this will be recertified on an annual basis and if the number of assessments falls below three in a three month period.

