The ENVIS-ion study will add to the current knowledge in the field by identifying whether aspirin treatment can influence the development and progression of white matter hyper-intensities which in-turn influence cognitive function. Importantly, it will determine whether retinal vascular imaging, a much less expensive approach, may be an alternative approach to MRI measurement. Clinically this may result in a low cost alternative to identify whether older people who may benefit from aspirin therapy, should be treated. Whilst there are a number of ongoing trials exploring the changes in white matter lesions and associations with cognitive function in ageing, none are looking at the association between retinal vascular imaging and MRI changes over time and their relationship with cognitive function [45].

A potential limitation of the study is that it will only provide information on people who reach the age of 70 years free from manifest cardiovascular disease and cancer, although most individuals will probably have subclinical atherosclerosis. However, given the increases in lifespan projected over the future decades, this is likely to represent an ever-increasing number of older people. The three year follow-up may be considered as a limitation; however it may also be optimal for the effects of aspirin to be demonstrable on the vasculature while minimizing potential loss to follow-up.

Lifestyle or pharmacological interventions that minimize decline in cognitive performance are urgently required. Aspirin is an appealing therapeutic candidate given its universal availability, community acceptance and low cost, all of which ensure equity and would facilitate community uptake. Equally, analyses of the brain and automated retinal imaging results from this trial will inform guidelines for health professionals where currently uncertainty exists. The ENVIS-ion trial will significantly inform global efforts to maximize our abilities to "maintain the brain" and, in addition, may improve the understanding of the mechanisms at the level of brain and vascular structure that underlie the effects of aspirin on cognitive function.

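### Aim (f) covers the MRI, retinal and cognition associations, but the Aim 6 analysis tests only modification of treatment effects

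*Protocol article*

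**What the plan says.** The section "The ENVIS-ion trial" lists six lettered aims. Aims (a) and (b) concern the effect of aspirin on MRI and retinal vascular imaging (RVI) measures. Aims (c), (d) and (e) are associations: RVI change with MRI change, baseline cognition with baseline MRI and RVI, and cognitive change with MRI and RVI change. Aim (f) is to determine whether "factors such as age, gender, education or blood pressure influence the above associations". The Abstract states a similar aim, without education.

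The Statistical analysis section uses the numbers 1 to 6, which match (a) to (f) in order and content:

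- Aims 1, 2 and 5: "analysis of covariance (ANCOVA) adjusting for baseline values (Aims 1,2 & 5").
- Aims 3 and 4: "Correlation and regression analysis will be used to determine the association between changes in MRI and RVI measures", and in the same sentence "the association of baseline cognitive measures with MRI and RVI parameters (Aims 3 & 4").
- Aim 6: generalized linear models of whether age, gender, education, previous aspirin use and hypertensive status "modify the treatment effects on MRI and RVI outcome measures (Aim 6").

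The Cognitive testing section adds that the CES-D depression scale "is also included in the ASPREE battery for later analysis as a covariate".

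**The concern.** Aim (f) and the analysis assigned to it have different targets. The aim concerns the associations, while the analysis concerns the treatment effects. The factors therefore reach aims (a) and (b) but not (c) to (e), the aims that are associations in the ordinary sense.

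The article's own background makes those factors plausible shared causes. The Rationale section says that cognitive performance declines with age even in healthy older adults. The Background section on MRI reports from a cited cohort that "the incidence of SBI increased markedly with age". The Background section on retinal imaging describes retinal vessel changes as markers of chronic hypertension, and the Discussion says that retinal changes mirror cerebral ones in ageing. The background also reports that a cited cohort found the link between retinal changes and cognition to be independent of traditional risk factors, so the article treats independence as informative.

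The Discussion then says of the trial that "it will determine whether retinal vascular imaging, a much less expensive approach, may be an alternative approach to MRI measurement". If an association mostly reflected age or blood pressure, retinal imaging might add little to what is already known about the person. The stated analyses would not show this.

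**Working it through.** **Step 1. Aims and analyses side by side**

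| Aim | Content | Stated analysis | Role of age, gender, education, blood pressure |
|---|---|---|---|
| (a), (b) / 1, 2 | Aspirin effect on MRI, RVI | ANCOVA with baseline value | Modifiers, through Aim 6 |
| (c) / 3 | RVI change with MRI change | Correlation and regression | None stated |
| (d) / 4 | Baseline cognition with MRI, RVI | Correlation and regression | None stated |
| (e) / 5 | Cognitive change with MRI, RVI change | ANCOVA with baseline value | None stated |
| (f) / 6 | Influence of the factors on the above | Models of treatment-effect modification | Reaches (a) and (b) only |

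The mismatch is visible from the text and needs no arithmetic. The steps below show how much it could matter.

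**Step 2. Inputs**

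The article gives no power or sample size for the association aims, so there is no figure of its own to reproduce. Two values of n are used: 600, the planned enrolment, and 460 = 2 × 230, the stated minimum per arm for the primary hypothesis. The article gives no correlation of age with any measure. The values 0.2, 0.3 and 0.4 are assumptions.

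**Step 3. Correlation induced by age alone**

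If age is the only link between measures X and Y, then r(X,Y) = r(age,X) × r(age,Y), and the partial correlation given age is zero. The two-sided 5% rejection probability by Fisher z is

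Φ(atanh(r)·√(n−3) − 1.96) + Φ(−atanh(r)·√(n−3) − 1.96).

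Example for 0.3 × 0.3 = 0.09 at n = 600: atanh(0.09) = 0.0902, times √597 = 24.43, gives 2.205. Then Φ(0.245) = 0.597, and the second term is negligible.

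| Age correlation with both | Induced r | Rejection, n = 460 | Rejection, n = 600 |
|---|---|---|---|
| 0.2 | 0.04 | 13.7% | 16.5% |
| 0.3 | 0.09 | 48.8% | 59.7% |
| 0.4 | 0.16 | 93.2% | 97.6% |

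The critical r is 0.091 at n = 460 and 0.080 at n = 600. The largest induced value, 0.16, is 0.16² = 2.6% shared variance.

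**Step 4. Correlation induced by treatment**

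For two equal arms with no correlation within arm, and a shift of d SD on both measures, r = (d²/4)/(1 + d²/4). With a continuous outcome, 230 per arm at 90% power detects d = (1.960 + 1.282)·√(2/230) = 0.302. Then r = 0.0228/1.0228 = 0.022. At n = 460 the rejection rate is 7.7% by formula and 7.9% in 4,000 simulated trials, and 4.6% in simulation with an arm term. With d = 0.2, r = 0.010; with d = 0.5, r = 0.059. Reaching the critical r through treatment alone needs about 0.63 SD on both measures at n = 460, or 0.59 SD at n = 600. At baseline the treatment route does not exist.

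**The case against.** A reader might infer that the associations will be run pooled over arms and unadjusted. The documents do not say so. The word regression allows covariates, CES-D is named as a later covariate, and Aim 5 is placed under a baseline-adjusted ANCOVA. This is a condensed article, and covariate lists are commonly left to the full protocol or analysis plan, which is not shown. That objection stands, and silence on covariates is not the point made here.

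A reader might also infer that treatment confounds the change associations. Step 4 shows this to be minor at the effect that 230 per arm would detect, and it cannot apply to Aim 4.

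The age figures are open to challenge too. They rest on assumed correlations, and the lower age limit of 70 narrows the age range. The background section on retinal imaging looks for changes that are highly correlated, and r of at most 0.16 would not meet that. For the question in aim (c), whether the changes run parallel, the raw correlation is a legitimate estimate. All of this stands, so the rejection rates are an illustration and not a forecast.

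Finally, aim (f) asks whether factors influence the associations, which is not the same as asking for confounder adjustment. That is fair, and it is why the fix has both adjusted estimates and interaction terms. It does not remove the mismatch, because the Aim 6 models provide neither for aims (c) to (e). The Aim 6 sentence names its factors and its target, and that target is narrower than the aim.

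**Conclusion.** The point holds as a mismatch within the article: the stated Aim 6 analysis does not answer aim (f) for the associations in (c) to (e). This rests only on the two sections read together.

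How much it matters depends on assumptions. With age correlations of 0.3 or more with both measures, age alone would produce a significant correlation in about half or more of trials of 460 to 600 people; at 0.2 it would do so in about one in seven to one in six. The risk is clearest for the baseline associations (Aim 4), since age may correlate less with three-year changes than with levels. A small correlation of this kind would be significant without showing that retinal imaging can stand in for MRI.

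The point does not support a claim that the plan states pooled or unadjusted analyses, or that confounding by treatment is material. It concerns the association aims and leaves the comparison of aspirin with placebo untouched. It is worth correcting because the Discussion's reading of retinal imaging depends on these aims.

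**What to change.** Extend the Aim 6 sentence in the Statistical analysis section so that its models also cover aims (c) to (e). For each association:

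- Report the raw correlation and, beside it, a regression or partial correlation adjusted for age, sex, education and blood pressure.
- Add CES-D where cognition is in the model.
- For change measures, add a treatment-arm term as a minor precaution.
- Include interaction terms for the aim (f) factors, so that their influence on the association is tested as the aim states.

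No new data are needed. Table 1 lists education and blood pressure, the Cognitive testing section lists CES-D, age is used for eligibility and stratification, and gender is already in the Aim 6 models. If each factor enters as one term, the cost is up to 4 + 1 + 1 main effects and 4 interactions, or 10 degrees of freedom out of roughly 460 to 600, plus a little more analysis and reporting.
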